#### Sample size and statistical considerations

### Randomized controlled trial

Randomization will be conducted centrally. Concurrent randomization to either the IRE or control arm will take place at the completion of 3-month modified FOLFIRINOX administration, at participating sites, and be stratified by the response following 3 months of treatment with mFOLFIRINOX (responder vs. stable disease), planned type of IRE procedure (open or percutaneous) and planned post-procedure treatment (chemotherapy versus radiotherapy/ chemotherapy versus observation). A total of 444 Intent-to-treat population (ITT) subjects (with 222 subjects in each arm) are required for at least 80% power for the primary efficacy endpoint (OS), with the expectation that there will be a total of 380 events in both arms. With the consideration of up to 16% attrition rate in both arms, and assuming a median survival of 12 months and exponential survival, up to 528 subjects (with 264 subjects per arm) will need to be randomized.

The sample size consideration for the primary endpoint OS was based on the assumptions that 1) there will be a 1:1 randomization scheme, 2) median survival will be 12 months and 16 months in the control and the IRE arm, respectively, i.e., a hazard ratio of 0.75 for IRE versus control 3) there will be a 5% 2-sided type I error, 4) there will be an accrual period of 36 months and follow-up period of 24 months after the study is fully enrolled. In addition, based on an assumption that median times to PFS will be 6 months and 8 months in the control and IRE arm, respectively, the study has at least 80% power for analysis of the difference in the secondary endpoint of time to PFS between the IRE and control arms.

### Registry study

The registry study will enroll 266 patients in the IRE cohort and 266 patients in the SOC cohort in order to achieve 90% power for analyzing both the OS and PFS endpoints. The power calculation assumes that it will take 24 months for accrual, and all 532 patients will be followed for at least 3 months after completion of accrual. The sample size consideration was based on the assumptions that the median OS time will be 12 months for SOC cohort and 18 months for the IRE cohort and there will be a 0.05 Alpha level (Type I error rate). For the secondary effectiveness endpoint of PFS, 210 patients will be needed per cohort for 90% statistical power assuming a median PFS of 8 months and 12 months for the SOC and IRE cohorts, respectively, or 116 patients per cohort if the median PFS survival is 8 months for the SOC cohort and 14 months for the IRE cohort.

#### Statistical analysis

### Randomized controlled trial

There will be three analysis populations: 1) an Intent-to-treat population (ITT) which includes all subjects randomized with treatment assignment based on randomization (regardless of actual treatment received); 2) a Modified Intent-to-treat population (mITT) which includes randomized subjects in the control arm who did not receive IRE procedures, and those in the IRE arm who have undergone the IRE procedure, excluding subjects with major protocol deviations. Treatment assignment will be based on the randomized treatment. For subjects who are randomized to control arm but later received IRE treatment, the study data only up to the date of IRE will be considered in this analysis population. Those subjects randomized to the IRE arm but did not receive IRE procedures will be excluded from this analysis population; and 3) a Safety Population consisting of all randomized subjects. If subjects randomized to the control arm receive IRE treatment with NanoKnife, they will be included in the IRE safety population. Similarly, if subjects randomized to the IRE arm did not receive IRE treatment, they will be included in the control safety population.

For the primary efficacy endpoint, the null hypothesis for OS is stated as H_0_: S_control_ = S_IRE_ and the alternative hypothesis is H_1_: S_control_ ≠ S_IRE_, where S_control_ is the median OS time for the control arm, and S_IRE_ is the median OS time for the IRE treatment arm.

The null hypothesis states that there is no difference in median OS time post randomization between the IRE arm and the control arm, while the alternative hypothesis states there is. The trial is powered to show the superiority of OS of 4 months in the IRE arm over the control arm. The above null hypothesis will be tested by a 2-sided log rank test at 0.05 significance level in the final analysis. If the null hypothesis is rejected by the two-sided test and the observed median OS time in the IRE is greater than in the control arm, the alternative hypothesis will be established and the superiority of OS in the IRE arm will be statistically proven.

For the secondary efficacy analysis, the null hypothesis for PFS is H_0_: μ_control_ = μ_IRE_ with the alternative hypothesis being H_1_: μ_control_ ≠ μ_IRE_,where μ_control_ is the median PFS time for the control arm, and μ_IRE_ is the median PFS time for the IRE arm. This study is powered to show the superiority of PFS of 2 months in the IRE arm over the control arm. The above null hypothesis will be tested by a 2-sided log rank test at 0.05 significance level only if the result of testing the primary efficacy endpoint is statistically significant. If the above null hypothesis is rejected by the two-sided test and the observed median PFS time in the IRE is greater than in the control arm, the alternative hypothesis will be established and the superiority of the PFS in the IRE arm will be statistically proven.

Analysis of the primary efficacy endpoint and key secondary endpoints will also be performed for the mITT population as supportive analyses. Safety analysis will be performed on the Safety population. To control the overall type I error rate for testing efficacy endpoints, a fixed-sequence testing procedure will be used to test the primary and secondary efficacy endpoints in a predefined order. The test will be performed in sequence and significance of OS endpoint is required in order to proceed to the testing of PFS endpoint. All statistical tests will be at the two-sided 0.05 significance level and the corresponding *p*-values and 95% confidence intervals (CIs) will be reported. Subjects alive or lost to follow-up at the time of analysis will be censored at their last date of follow-up. In the final analysis, OS will be compared between the randomized treatment arms using a two-sided log-rank test at a type I error rate of 0.05. ITT analysis will be the primary analytic methods, supported with mITT and Cox proportional hazards analysis. Kaplan-Meier methods will be used to summarize survival distribution of OS and median OS time for each treatment arm. The relative treatment effect between the IRE arm and the control arm with respect to OS will be estimated by the hazard ratio (HR) and the associated two-sided 95% CIs using the Cox proportional hazards model.

There will be one planned interim analysis with an early stopping rule for adverse events and for superiority associated with the primary efficacy endpoint. Stopping rules for adverse events will include (but will not be limited to) two IRE related ventricular arrhythmias during the IRE procedure that require synchronized cardioversion or defibrillation or one death determined by the investigator and the Data Monitoring Committee (DMC) to be related to IRE.

There will be a single OS-based threshold for stopping the trial for superiority using a pre-specified Haybittle-Peto boundary with an alpha level of 0.001. If the IRE arm demonstrates superiority over the control arm with *P*-value< 0.001 following the interim analysis, the study may be terminated early, depending on the safety profile. Since the study will be powered based on an OS primary endpoint, there will not be an adverse events related threshold for stopping the trial for superiority.

The interim analysis will not be used to lead to early termination of the study because of futility (e.g., the IRE arm does not demonstrate superiority over the control arm). The DMC will have the ability to make recommendations after reviewing the results of the interim analysis or through safety monitoring, and in conjunction with the study sponsor, can decide to continue or terminate the study to save resources.

The interim analysis will be conducted when approximately 251 (66% of the total 380) deaths have been observed in the overall ITT population. As part of the interim analysis, the assumptions about the sample size estimation will also be evaluated. The final analyses of OS will be conducted at the 5% level of significance when approximately 380 death events occurred. Interim data will be evaluated by the independent DMC.

Subjects who do not have disease progression and have not died, will be censored at the date of last tumor assessment. Subjects with a single missing radiologic or clinical assessment immediately prior to a visit with documented disease progression (or death) will be analyzed as a PFS event at the time of the clinical or radiologic assessment that shows progression. Subjects with two or more consecutive missing radiologic or clinical assessments immediately prior to an assessment without documented progression (or death) will be censored at the date of last assessment when the subject was documented as progression-free prior to the first of the two or more missing assessments. PFS will be analyzed using similar statistical methods as that for the OS endpoint.

Pain Severity Scores and average Pain Interference Score will be derived for each subject from BPI-SHORT FORM questionnaire. QOL measures will be derived for each subject from the EQ-5D questionnaire, including the EQ Visual Analogue Scale (VAS) and EQ-5D summary index. Both absolute change and percent change from baseline will be analyzed by treatment arm and by study visit for all of the above.

For the primary safety endpoints, a log-rank test will be used to compare the time (in months) from randomization to death or new onset of Grade 4 AEs for the two treatment arms, with data censored at the time of loss to follow up or study discontinuation. The number and proportion of subjects with a high-grade complication defined as any AEs or SAEs with a CTCAEv5.0 grade of 3 or higher will be summarized by treatment arm and CTCAE grade.

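### The time-to-death-or-Grade-4 safety test starts its clock at randomization but groups subjects by treatment received later, which biases that test toward IRE

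*Protocol article*

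**What the plan says.** All references are to the protocol article.

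- **Endpoint and test.** Study endpoints and assessments makes time from randomization to death or new Grade 4 adverse event a co-primary safety endpoint. Statistical analysis, Randomized controlled trial, applies a log-rank test to "compare the time (in months) from randomization to death or new onset of Grade 4 AEs for the two treatment arms".
- **Population.** The same section assigns safety analysis to the Safety population, which holds all randomized subjects but moves them in both directions: "If subjects randomized to the control arm receive IRE treatment with NanoKnife, they will be included in the IRE safety population"; and "if subjects randomized to the IRE arm did not receive IRE treatment, they will be included in the control safety population".
- **Supportive mITT.** Randomized labels are kept, but "Those subjects randomized to the IRE arm but did not receive IRE procedures will be excluded from this analysis population". Its definition first admits only control subjects without an IRE procedure. It then adds a rule for crossovers: "For subjects who are randomized to control arm but later received IRE treatment, the study data only up to the date of IRE" is used.
- **Role of each population.** ITT is primary for OS and mITT is supportive.

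No landmark, time-dependent exposure or safety comparison by randomized arm is stated.

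**The concern.** Group membership in the safety test is decided after time zero, by something only survivors can experience. Two moves follow.

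1. An IRE-arm subject who dies while waiting for the procedure becomes a control subject with a very early event.
2. A control subject who lives long enough to cross over becomes an IRE subject and brings along all the event-free time before the procedure.

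Both lower the apparent event rate in the IRE group and raise it in control, even if IRE does nothing. The endpoint includes death, so the usual tolerance for as-treated grouping in adverse event tables does not carry over to it.

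Safety against control is a primary objective of the trial, and the interim rule lets early termination for superiority depend on the safety profile. A nominally significant result in favour of IRE on this endpoint could therefore carry weight without meaning anything.

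**Working it through.** **The plan's own figures first.** Inputs from Sample size and statistical considerations: "there will be a 5% 2-sided type I error", at least 80% power, "a hazard ratio of 0.75 for IRE versus control", medians 12 and 16 months, 36 months of accrual plus 24 of follow-up.

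- Schoenfeld events: 4 × (1.960 + 0.842)² / (ln 0.75)² = 380 after rounding up (stated 380).
- Event probabilities 0.895 and 0.821, mean 0.858: 380 / 0.858 = 443 (stated 444).
- 444 / (1 − 0.16) = 529 (stated 528).

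The design figures reproduce and are not in dispute.

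**Assumptions for the bias.** No true effect; median 12 months in both arms; 264 per arm; wait to IRE uniform from 0 to W months; only death prevents IRE. The waits and the crossover rate are assumed, because the article gives none.

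**Step 1, per arm.** Hazard λ = ln 2 / 12 = 0.0578 per month. Probability that death is observed: 1 − (e^(−24λ) − e^(−60λ)) / (36λ) = 1 − (0.2500 − 0.0313) / 2.079 = 0.895. Deaths: 264 × 0.895 = 236.2. Person-months: 236.2 / λ = 4,090.

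**Step 2, IRE-arm deaths before the procedure.** q = 1 − (1 − e^(−λW)) / (λW). The number moved is k = 264q, with about W/3 months of follow-up each.

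**Step 3, rate ratio in the Safety population, no crossover.** For W = 2, k = 14.7, carrying 9.6 person-months: [(236.2 − 14.7) / (4,090 − 9.6)] / [(236.2 + 14.7) / (4,090 + 9.6)] = 0.0543 / 0.0612 = 0.89.

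**Step 4, add crossover.** Assume a crossover hazard of 0.01 per month in the first 12 months. Share of control crossing: 0.01 / 0.0678 × (1 − e^(−12 × 0.0678)) = 8.2%, or 21.7 subjects. They bring 5.2 months each before IRE, and 85.5% later die on study: 18.5 deaths and 21.7 × 5.2 + 18.5 / λ ≈ 434 person-months. For W = 2: [(236.2 − 14.7 + 18.5) / (4,090 − 9.6 + 434)] / [(236.2 + 14.7 − 18.5) / (4,090 + 9.6 − 434)] = 0.0532 / 0.0634 = 0.84.

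| Maximum wait W | IRE arm dying first | Ratio, no crossover | Ratio, about 8% crossover |
|---|---|---|---|
| 0.5 month | 1.4% (3.8) | 0.97 | 0.92 |
| 1 month | 2.8% (7.5) | 0.94 | 0.89 |
| 2 months | 5.6% (14.7) | 0.89 | 0.84 |

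The true ratio is 1.00 in every cell.

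**Step 5, simulation of the same set-up.** Simulated trials of 528 subjects give hazard ratios of about 0.97 to 0.88 without crossover, with 4% to 30% significantly favouring IRE. With about 8% crossover they give about 0.93 to 0.84, with 12% to 48%. A further check with 2,000 replicates per cell gave 5%, 12% and 25% without crossover, and 18%, 23% and 47% with it. Its hazard ratios match the table to within about 0.01. Analysis by randomized arm gave about 1.00 and 2% to 3%.

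**Step 6, sensitivity.**
- Adding Grade 4 events (median 18 months to Grade 4, wait 0.25 to 1.5 months) weakens the bias slightly: 0.86 becomes 0.88 with 10% of controls intended to cross over, and 0.81 becomes 0.83 with 20%.
- If poor-prognosis controls cross over, the Safety ratio stays below 1, at 0.88 to 0.94.
- With a true 10% procedural Grade 4 risk and 20% intended crossover, randomized arms give 1.09 and the planned grouping gives 0.92.
- The proportion with a Grade 3 or higher event moves the other way: about 0.52 IRE against 0.46 control as treated, when the randomized arms are both 0.49. Subjects labelled IRE live longer and have more time to report events.

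**Step 7, mITT.** The IRE arm loses its early deaths and control keeps its own. For W = 2: 0.0543 / (236.2 / 4,090) = 0.94. For W = 1: (228.7 / 4,087.5) / (236.2 / 4,090) = 0.97. A wait of 0.5 to 3 months gives about 0.90. Poor-prognosis crossover, censored at IRE, moves the ratio to between 0.95 and 1.00.

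**The case against.** Several points on the other side stand.

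- **Efficacy.** A reader might infer that the OS claim is biased. It is not: OS is tested in ITT by randomized arm, PFS is tested only after OS succeeds, and the interim counts deaths in ITT. Only the supportive mITT is touched, and it moves nobody between arms.
- **IRE looks safer throughout.** This does not follow. The Grade 3 or higher proportion can move against IRE.
- **Larger bias figures.** With a composite median of 6 months and a wait of up to 2 months, ratios of 0.82 (61% false benefit), or 0.77 (83%) with crossover, can be produced. They require that any Grade 4 event before the procedure permanently prevents IRE, which the article does not say. If only death prevents it, the same model gives about 0.90 to 0.91 (20% to 22%) and 0.86 to 0.87 (38%).
- **Hidden procedural harm.** As-treated grouping keeps every recipient's procedural events in the IRE group, high-grade events are also tabulated, and the adverse event stopping rules act on IRE-related events whatever the grouping. No safety success criterion is stated and alpha control is described for efficacy, so the false-benefit rates describe a nominal test and not a wrong decision under a stated rule.

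Two objections do not remove the point. As-treated grouping is customary for adverse event tables, but that does not validate a log-rank test from randomization on an endpoint that includes death. The test sentence speaks of two treatment arms, which could mean the randomized arms; but the same section sends safety analysis to the regrouped population, so if randomized arms are meant, the text must say so.

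**Conclusion.** The concern holds for one test: the log-rank comparison of time to death or new Grade 4 event. Its direction follows from the stated rules, and it favoured IRE in every null scenario run. Its size is not known. On a death-only null model with a maximum wait of 0.5 to 2 months, the hazard ratio is about 0.97 to 0.88 without crossover and about 0.93 to 0.84 with about 8% crossover, so the bias runs from slight to substantial. The sign can reverse when procedural harm is real, but that result rests on an assumed 10% procedural risk and 20% intended crossover.

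The mITT issue is separate and minor. The null OS ratio is about 0.97 to 0.94 for a 1 to 2 month maximum wait, lower with longer waits, and possibly offset by informative censoring of crossovers. Its definition also both excludes control crossovers and uses their data up to IRE.

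**What to change.** 1. Make the primary comparison of time to death or new Grade 4 event by randomized arm, in all randomized subjects.
2. Add an analysis with IRE as a time-dependent exposure from the procedure date. It is needed because the randomized comparison charges crossovers' procedural events to control, the small downside of item 1. It is not protected by randomization: with prognosis-related crossover its null rate ratio ranged from about 0.84 to 1.11, so it should complement item 1 and not replace it.
3. Keep as-treated grouping for descriptive adverse event tables, and note that follow-up differs between the groups.
4. For mITT, either retain IRE-arm subjects who did not reach IRE or apply one fixed landmark to both arms. State a single rule for control crossovers. Do not present mITT as independent support for OS or PFS.

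The cost is protocol and SAP wording and modest programming. The randomization date and the IRE date are already needed for the rules as written, so no new data and no change in sample size are required.

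### The RCT releases PFS at the full two-sided 0.05 once OS is significant, but neither limits PFS to the final analysis nor sets a PFS level for the interim look at which OS may already be significant

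*Protocol article*

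**What the plan says.** All of this is in the Protocol article, Statistical analysis, Randomized controlled trial.

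- **Gate and level for PFS.** PFS is "tested by a 2-sided log rank test at 0.05 significance level only if the result of testing the primary efficacy endpoint is statistically significant". The multiplicity paragraph repeats that "significance of OS endpoint is required in order to proceed to the testing of PFS endpoint" and that "All statistical tests will be at the two-sided 0.05 significance level".
- **Claim of control.** "To control the overall type I error rate for testing efficacy endpoints, a fixed-sequence testing procedure will be used".
- **Direction of the claim.** PFS superiority is declared only if the log-rank test rejects and "the observed median PFS time in the IRE is greater than in the control arm".
- **Two looks for OS.** The interim falls at about 251 of 380 deaths, "using a pre-specified Haybittle-Peto boundary with an alpha level of 0.001". If OS crosses, "the study may be terminated early, depending on the safety profile". Otherwise, "The final analyses of OS will be conducted at the 5% level of significance", at about 380 deaths.

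The interim paragraphs describe one threshold, for OS. They neither mention a PFS test nor rule one out.

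**The concern.** A fixed sequence at full level protects the second endpoint when there is a single analysis. When the first endpoint can be significant at either of two looks, the second needs one fixed analysis time or its own boundary at each look. The article gives neither.

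Two paths are left open. If OS crosses and the trial stops, the interim data are the last data, the gate is open, and 0.05 is the only PFS level in the text. If OS crosses and the trial continues, nothing prevents a PFS test at 0.05 at the interim and another at the final.

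PFS is the only secondary endpoint with a confirmatory superiority claim, so the article's statement of error control matters for it. The excess arises when IRE truly prolongs survival, which is the case the trial is designed for.

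**Working it through.** **Inputs from the article:** OS hazard ratio 0.75 (medians 12 and 16 months); 380 deaths; two-sided 0.05; interim at 251 deaths with level 0.001; 444 ITT subjects; accrual 36 months plus 24 months of follow-up; PFS medians 6 and 8 months.

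**Assumptions not in the article:** correlation ρ between the OS and PFS log-rank statistics, taken as 0.5-0.9; PFS information at the interim, taken as 71-81% of the final. The latter is consistent with the article's inputs. With uniform accrual, exponential times and 444 subjects, 251 deaths are reached at about month 37, with about 338 of an eventual 432 PFS events, and 338/432 = 0.78.

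**Step 1. Reproduce the plan's event number.** Events = 4(1.960 + 0.842)² / (ln 0.75)² = 379.4, so 380, as stated. Power with 380 events is 0.801.

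**Step 2. OS on its own.** Critical values are 3.291 (0.001) and 1.960 (0.05), and the two OS statistics have correlation √(251/380) = 0.813. The overall two-sided error is 0.0501, so OS is not the problem.

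**Step 3. Chance that OS crosses at the interim under the design effect.** Expected Z at the final = |ln 0.75| × √380 / 2 = 2.804. At the interim it is 2.804 × 0.813 = 2.279. P(cross) = 1 − Φ(3.291 − 2.279) = 1 − Φ(1.012) = 0.156.

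**Step 4. PFS error with no true PFS effect and OS hazard ratio 0.75.** The OS and PFS statistics at both looks are treated as jointly normal (4 million draws per case). The directional condition makes 2.5% the nominal error of a claim favouring IRE. Ranges are over PFS information of 71-81%.

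| ρ | One test, at the look where OS crosses: favouring IRE | Same, two-sided | Tests at both looks: favouring IRE | Same, two-sided |
|---|---|---|---|---|
| 0.5 | 2.6-2.7% | 3.5-3.6% | 3.0-3.2% | 3.9-4.1% |
| 0.7 | 2.7-2.8% | 3.1-3.2% | 3.3-3.5% | 3.7-3.8% |
| 0.9 | 2.7-2.8% | 2.7-2.8% | 3.5-3.7% | 3.5-3.8% |

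A different but equally plausible correlation between OS at one look and PFS at the other moves the single-test figure to as much as 2.9%.

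**Step 5. Larger OS effects.** With a final OS drift of 4.05 (hazard ratio exp(−2 × 4.05/√380) = 0.66), OS crosses at the interim in half of trials. With tests at both looks, two-sided PFS error is then 5.5-5.8% (ρ 0.5-0.7, 75% information). In the limit where OS always crosses early, it is 7.0-7.5% two-sided and 3.5-3.8% favouring IRE.

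**Step 6. Same model under possible rules.**

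- PFS tested at the final only: 2.5% favouring IRE.
- PFS at 0.001 at the interim and 0.05 at the final: 2.5%.
- O'Brien-Fleming-type interim level (0.016-0.026 two-sided) with the final left at 0.05: up to 2.7-2.8%. The final level would have to fall to about 0.043-0.045.

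**The case against.** A reader might infer that the plan does test PFS at whichever look OS becomes significant, or tests it twice, and so fails to control error at the level it claims. The article does not say this. The OS hypothesis test is placed in the final analysis, the PFS test follows in the same form, and the interim's superiority purpose is confined to OS. On a final-only reading there is no inflation.

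The article's stated level is also two-sided 0.05. On that scale the design-effect error stays below 5% even with tests at both looks. The 2.5% benchmark comes from the directional condition on the claim and is not a figure in the text. The excess further needs an early OS crossing (15.6% at the design effect) and no PFS effect alongside a real OS benefit, although the plan expects a PFS benefit and deaths without progression count as PFS events. Finally, the full protocol or SAP may name the look.

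Most of this stands, and it makes the point conditional and modest. It does not remove it. The article does more than stay silent: it fixes 0.05 for every test, opens PFS on OS significance, allows that significance at an interim, and asserts overall control. If the trial stopped at the interim, the only PFS test those statements allow would use interim data at the full level. Type I error is by definition assessed with no PFS effect, so the expected benefit is no defence.

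**Conclusion.** The point holds conditionally. The stated rules do not by themselves secure the error control claimed for PFS, because they leave open a full-level PFS test at the interim. If that test is made, the error in favour of IRE at the design OS effect is about 2.6-2.9% with one test and about 3.0-3.7% with tests at both looks, against 2.5%. These figures rest on the assumed correlation (0.5-0.9) and PFS information (71-81%). Two-sided error exceeds 0.05 only with tests at both looks and an OS effect larger than designed. OS is unaffected. The excess is modest, but it bears on a confirmatory claim and should be settled before the interim.

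**What to change.** In the secondary-efficacy and interim-analysis paragraphs, state that an OS crossing at the interim does not release the full 0.05 for PFS at that look. Then choose one rule:

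- Test PFS once, at the final analysis, defined as the one at about 380 deaths, so that a stopped trial's interim does not become the final by default.
- If OS crosses at the interim, test PFS there at p<0.001, and use 0.05 at the final.

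If an O'Brien-Fleming-type spending function on PFS events is preferred, the final PFS level must be lowered to match (about 0.043-0.045 at 71-81% information).

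If the full protocol or SAP already contains such a rule, the article's wording only needs to be aligned with it. The cost is one or two sentences and no extra patients. The downside is that a PFS claim becomes harder to obtain if the trial stops at the interim, and under the final-only rule there would then be no confirmatory PFS test.

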### Registry study

There will be two analysis populations including 1) an Effectiveness Population which consists of all enrolled patients who will be matched by propensity score quintiles, all of whom have received at least 3 months of therapy per SOC without evidence of disease progression, and 2) a Safety Population which consists of all enrolled patients with the cohort assignment based on the actual treatment received.

For the primary efficacy endpoint, the null hypothesis for OS is stated as H_0_: S_soc_ = S_IRE_ and the alternative hypothesis is H_1_: S_soc_ ≠ S_IRE_, where S_soc_ is the median OS time for the SOC cohort, and S_IRE_ is the median overall survival time for the IRE cohort. For the secondary efficacy analysis, the null hypothesis for PFS is H_0_: μ_soc_ = μ_IRE_ with the alternative hypothesis being H_1_: μ_soc_ ≠ μ_IRE_, where μ_soc_ is the median PFS time for the SOC cohort, and μ_IRE_ is the median PFS time for the IRE arm. The null hypothesis for each state that there is no difference in median OS or PFS time post the initial 3 months of therapy between the IRE cohort and the SOC cohort, while the alternative hypothesis states there is. This study is powered to show the superiority of OS and PFS in the IRE cohort over the SOC cohort. The above null hypotheses will be tested by a 2-sided log rank test stratified by propensity score quintiles at the 0.05 significance level. The PFS endpoint will be tested only if the result of testing the primary effectiveness endpoint is statistically significant. Exploratory subgroup analyses will include patient’s sex (male or female), and other factors to be determined after the study team reviews the final analyses of primary and secondary endpoints.

There will be one planned interim analysis for the registry study, to be conducted when 50% of 266 patients in either cohort die, or per the recommendation of the DMC. The purpose of the interim analysis is to examine accrual rate and check the assumptions about the median survival times (i.e., 12 months for SOC cohort and 18 months for the IRE cohort), to ensure that the study will have sufficient power for planned analyses.

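### The RCT randomizes within three stratification factors but states its OS and PFS log-rank tests and its Cox model without strata: valid, but it forgoes power if those factors are at least moderately prognostic

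*Protocol article*

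**What the plan says.** In the protocol article, under Sample size and statistical considerations (Randomized controlled trial), central randomization is to "be stratified by the response following 3 months of treatment with mFOLFIRINOX (responder vs. stable disease), planned type of IRE procedure (open or percutaneous"), with a third factor, "planned post-procedure treatment (chemotherapy versus radiotherapy/ chemotherapy versus observation").

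Under Statistical analysis (Randomized controlled trial), the tests and the estimate appear several times without strata or covariates:

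- OS, with the hypotheses: "The above null hypothesis will be tested by a 2-sided log rank test at 0.05 significance level in the final analysis".
- OS, in the description of the final analysis: "OS will be compared between the randomized treatment arms using a two-sided log-rank test at a type I error rate of 0.05".
- PFS, conditional on a significant OS result: "The above null hypothesis will be tested by a 2-sided log rank test at 0.05 significance level only if the result of testing the primary" endpoint is significant; and later, "PFS will be analyzed using similar statistical methods as that for the OS endpoint".
- The treatment effect on OS "will be estimated by the hazard ratio (HR) and the associated two-sided 95% CIs using the Cox proportional hazards model".

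Under Statistical analysis (Registry study), the corresponding hypotheses are "tested by a 2-sided log rank test stratified by propensity score quintiles at the 0.05 significance level".

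**The concern.** When allocation is forced into balance within strata, the usual analysis conditions on the same strata. If the strata predict survival and the log-rank test ignores them, the test treats between-stratum variation as noise that the design has already removed. It then rejects a true null less often than 5%. The Cox model without strata estimates an overall hazard ratio that lies nearer to 1 than the within-stratum ratio.

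The design has little reserve. It is sized for 80% power, and PFS can be tested only if OS succeeds, so power forgone on OS is also forgone on PFS. The article names strata for the registry test and not for the RCT test, which makes an unstratified RCT test the natural reading of the text.

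**Working it through.** **1. Number of cells.** Response (2) × planned approach (2) × planned post-procedure treatment (3) = 12.

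**2. The plan's own figures.** Inputs from Sample size and statistical considerations: medians 12 and 16 months, hazard ratio 12/16 = 0.75, two-sided 5%, 1:1 allocation, accrual 36 months, follow-up 24 months.

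- Events (Schoenfeld): d = 4(1.960 + 0.842)² / (ln 0.75)² = 4 × 7.849 / 0.08276 ≈ 379.4, so 380, as stated.
- Power at 380 events: Φ(√380 × 0.2877/2 − 1.960) = Φ(0.844) = 80.1%.
- Event probability with exponential survival and uniform accrual: 1 − (e^(−24λ) − e^(−60λ))/(36λ), λ = ln 2/median. This gives 0.895 (control) and 0.821 (IRE). Then 222 × (0.895 + 0.821) ≈ 381 events from 444 subjects, which agrees with the plan.

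These formulas contain no strata, and the 0.75 comes from arm-level medians. The stated 80% is therefore the power of an unstratified test at the overall hazard ratio, and it is correct.

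**3. What stratifying would change.** The article gives no stratum effects or shares, so these are assumptions: shares 40/60 (response), 60/40 (approach) and 60/25/15 (post-procedure treatment); 444 subjects; analysis at 380 deaths; permuted blocks of 4 within the 12 cells; 3,000 to 8,000 simulated trials per row (Monte Carlo error about 0.5 to 0.9 points). Stratum hazard ratios are listed as response / approach / two post-procedure levels.

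Within-stratum treatment hazard ratio 0.75:

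| Assumed stratum effects | Power, no strata | Power, 12 strata | Mean HR, no strata | Mean HR, 12 strata |
|---|---|---|---|---|
| None (1/1/1/1) | 80.3% | 78.4% | 0.749 | 0.749 |
| Weak (0.8/1/0.9/1.1) | 79.3% | 77.7% | 0.752 | 0.750 |
| Moderate (0.6/0.85/0.8/1.25) | 74.8% | 76.9% | 0.764 | 0.751 |
| Strong (0.45/0.7/0.7/1.6) | 70.0% | 79.2% | 0.778 | 0.746 |
| Very strong (0.33/0.6/0.6/2.0) | 58.1% | 77.1% | 0.803 | 0.751 |

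Overall hazard ratio about 0.75, which is how the plan frames it:

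| Assumed stratum effects | Within-stratum HR used | Power, no strata | Power, 12 strata |
|---|---|---|---|
| Moderate | 0.736 | 81.9% | 83.4% |
| Strong | 0.718 | 80.8% | 87.4% |

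The gain from stratifying is 76.9 − 74.8 = 2.1 or 83.4 − 81.9 = 1.5 points (moderate), and 79.2 − 70.0 = 9.2 or 87.4 − 80.8 = 6.6 points (strong). The cost is 80.3 − 78.4 = 1.9 points (none) or 79.3 − 77.7 = 1.6 points (weak).

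**4. Type I error.** With no treatment effect, the test without strata rejects in about 5% of trials when the factors are not prognostic, and in 4.3%, 3.3% and 2.5% under moderate, strong and very strong effects. The stratified test stays at 4.6 to 5.4%. Neither is inflated.

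**5. Sparse cells.** Under the assumed shares the smallest of the 12 cells holds 444 × 0.40 × 0.40 × 0.15 ≈ 11 subjects. Dropping planned approach leaves 6 cells, the smallest with 444 × 0.40 × 0.15 ≈ 27. With those 6 cells, the simulated cost when the factors have little or no effect is about 0 to 1 point.

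**The case against.** The strongest reply is that the point rests on silence in a condensed article. The article never calls the RCT test unstratified, the SAP is not shown, and strata and pooling rules often sit there. The registry contrast also proves less than it seems to. Propensity quintiles are what makes that non-randomized comparison possible, so the registry test could hardly be described without them, while the randomized test is valid either way. This stands as a limit: the SAP may already name the strata. It does not remove the point, because the article states the RCT tests repeatedly, with sidedness and alpha and always without the factors it randomizes by.

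The factors are also not called prognostic, and every stratum effect above is assumed. That stands too, and makes the loss conditional. With weak or no effects, stratifying on 12 cells loses a little power.

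A reader might infer that true power is below the stated 80%. The article does not support that. The 0.75 is the ratio of arm-level medians, and at an overall hazard ratio near 0.75 the unstratified test keeps about 81 to 82% in the simulations. The lower figures in the first table arise only if 0.75 is taken as the within-stratum ratio, and there the 12-cell test does not reach 80% either. Nor is the unstratified hazard ratio an error: it estimates a different quantity.

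**Conclusion.** The point holds as one of efficiency and of consistency between design and analysis. As written, the RCT's OS and PFS tests and its Cox model do not use the factors by which subjects are randomized. The stated test is valid, and the stated 80% power is right for it.

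What is forgone is power that stratified randomization could have supplied: roughly 1 to 3 points if the factors are moderately prognostic and 6 to 10 if they are strongly so. The very strong scenario shows a 19-point gap, but it rests on extreme assumed effects and on 0.75 being the within-stratum ratio. The hazard ratio moves toward 1 by about 0.01 (moderate) to 0.03 (strong). All these sizes depend on assumed stratum effects and shares. The direction does not, provided the factors are at least moderately prognostic.

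**What to change.** State that the log-rank tests for OS and PFS, and the Cox model, are stratified by the randomization factors, at both the interim and the final analysis. Add a rule, set in advance and without reference to outcome by arm, for pooling sparse cells; for example, drop planned approach first, which leaves response by planned post-procedure treatment. Keep the unstratified log-rank test as a sensitivity analysis. Settle this before the interim look at about 251 deaths, so that the choice cannot depend on the data. If the SAP already names strata, it is enough to bring the protocol wording into line with it.

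The cost is a few lines of text, with no change to sample size or event target. The statistical downside is about 0 to 2 points of power if the factors turn out not to be prognostic, and about 0 to 1 point with the pooled cells.
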